Assuming that 25% of study participants drop out after randomization and prior to the nine months follow-up, we will need to recruit 280 groups or 2,520 families. According to Statistics Denmark, 4,000 children were born in Aarhus in 2012. Since about 45% of all Danish live births were first born children, and assuming that 80% choose to participate in the research project, detecting such an effect size will roughly require a 1½ year trial; see also 3.A below.

Groups are considered as “did not receive intervention” if 50% of the mothers in a FSP group drop out or if more than two group meetings are cancelled due to group disagreement.

We consider women or men as dropouts from the program if they miss two consecutive meetings without reasonable reason or apologies (such as illness). We categorize women or men as “did not receive intervention” if they do not attend at least two of the postnatal sessions.

We will not base the continuation of recruitment on interim analyses. This is primarily because we expect the intervention to be associated with very low risk for participants. There may be smaller inconveniences, at least for some, associated with the level of time consumption from participating in a program such as FSP. Nevertheless, we will conduct interim analyses and report preliminary results when sample size allows for power of 0.80 to detect an effect size of 0.2 between conditions at the family-level (*N* = 800 families), ignoring group level variation. As explained, however, participation is entirely voluntary and will not affect access to other family services provided by the municipality or the region. Even if the program does not significantly improve participants’ primary outcome in short-term preliminary analyses, this will not lead us to discontinue the program thereby ignoring possible secondary, tertiary and longer term outcomes.

We will perform a dropout analysis that characterizes dropouts in terms of pre-intervention background variables (see list above) if more than 1/3 of study participants (mothers) drop out after initial randomization and prior to the nine months follow-up.

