### Blinding

The research team and families remain blind to study condition during recruitment, consent and baseline questionnaire, though blinding after this point in time is not possible.

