In order to test whether different subpopulations experience differential effects from FSP participation (tertiary outcomes), we will define subpopulations based on pre-randomization variables. The null hypothesis is that subgroups are affected equally by FSP participation. The alternative hypothesis is that subgroups experience differential effects. We will consider mothers with above high school education versus mothers with high school or below; mothers aged 23 or above versus mothers aged below 23; mothers who experienced previous psychiatric/therapeutic treatment versus mothers who did not; families who have experienced financial strain versus families who did not; and families with low relationship stability versus families with high stability. We will, in addition, consider subgroups recruited early (during first six months after study initiation), mid-period (during months 7–12), and late (after month 12). In practice, we will test for significance of subgroup-treatment interactions using t-tests and perform a joint F-test for significance of the entire set of interactions [47].

Because our study collects multiple outcomes, permutation testing methods, and a step-down procedure will be applied to account for the increased likelihood of false discoveries [48]. This is adopted in combination with a naïve evaluation strategy (which examines each outcome individually).

Exploratory analyses that in addition to pre-randomization controls include indicators for the identity of the responsible group leader will be performed to control for variation in program delivery across health visitors. Exploratory analysis will also investigate whether initial group composition affects family outcomes. We will define group composition in terms of the shares of the members of a FSP group that belong to the various subgroups detailed immediately above. Note that group composition by construction will be random conditional on due date and strata.

Finally, as described, we will perform a dropout analysis if more than 1/3 of study participants drop out after initial randomization and prior to the nine months follow-up. In practice we will run a logistic regression of a binary variable indicating dropout as the dependent variable with pre-randomization controls as the independent variables.

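### The dropout analysis leaves out study arm and runs only above one-third loss, although the plan expects 25%

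*Protocol article*

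**What the plan says.** The dropout analysis is described in two places in the protocol article.

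- **Purpose (2.E Sample size).** "We will perform a dropout analysis that characterizes dropouts in terms of pre-intervention background variables". The condition is "if more than 1/3 of study participants (mothers) drop out after initial randomization and prior to the nine months follow-up".
- **Model (Statistical methods).** The same threshold is repeated, without the restriction to mothers: "we will perform a dropout analysis if more than 1/3 of study participants drop out after initial randomization and prior to the nine months follow-up". The model follows: "we will run a logistic regression of a binary variable indicating dropout as the dependent variable with pre-randomization controls as the independent variables". The pre-randomization variables are listed earlier in that section: age, marital status, education, employment, previous psychiatric or therapeutic treatment, smoking, place of birth, siblings, welfare receipt, financial strain and social desirability. Arm is not listed, and because it is the result of randomization it cannot be read into the list.
- **Expected loss (2.E Sample size).** The allowance for loss reads "Assuming that 25% of study participants drop out after randomization and prior to the nine months follow-up". The recruitment target derived from it is 2,520 families in 280 groups.
- **Blinding.** Research team and families are blind up to the baseline questionnaire, "though blinding after this point in time is not possible".

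The primary outcome, PSOC at nine months, is a parent self-report collected by web survey, or by telephone if preferred. The only other attrition rule that refers to an arm stops the study if more than two thirds of women assigned to FSP drop out. It makes no comparison with TAU.

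**The concern.** A regression of dropout on baseline variables describes who leaves. What threatens a randomized comparison is loss at different rates in the two arms, or loss of different kinds of family in the two arms. The first needs arm in the model; the second needs arm-by-covariate terms. The stated model has neither.

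The trigger makes this worse. It lies above the loss that the plan itself expects, and it is pooled over arms, so a large imbalance can sit below it.

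Loss that depends on arm is plausible here. Families know their allocation, and FSP families are offered twelve further meetings with a permanent health visitor. What is at stake is the ability to judge whether the nine-month comparison among those with a PSOC score still reflects the randomized groups.

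The word dropout is also not settled. The sample size section defines dropping out of the program as missing two consecutive meetings, which cannot apply to TAU families.

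**Working it through.** **Inputs.** From 2.E Sample size: 2,520 families, expected loss 25%, trigger above 1/3, design effect size 0.20, between-group share of variance 0.20, power 0.80, significance level 0.05. Nine families per group (2,070/230). Allocation 1:1 from Randomization, so 1,260 per arm. A two-sided test is assumed, as sidedness is not stated.

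**1. The plan's own figure.** Individual randomization at effect size 0.20 needs 393 per arm, 786 in total. The design effect is 1 + (9 − 1) × 0.20 = 2.6, and 786 × 2.6 ≈ 2,044 families, or 227 groups. A cluster calculation with the noncentral t distribution gives 230 groups at power 0.802. The stated 230 groups and 2,070 families are reproduced.

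**2. Trigger against expectation.**
- Trigger: 2,520/3 = 840, so more than 840 losses are needed.
- Expected: 0.25 × 2,520 = 630.
- Standard error of the loss proportion with independent families: √(0.25 × 0.75/2,520) = 0.0086. The gap is (0.3333 − 0.25)/0.0086 ≈ 9.7 standard errors, and the exact binomial probability of passing 840 is about 3 × 10⁻²¹.
- With the variance inflated by 2.6, the gap is still about 6 standard errors.

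This assumes that true loss is the planned 25%. If it is well above that, the trigger can be met.

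**3. Imbalances below the pooled trigger (33.3%), equal arms.**
- 15% and 35%: pooled 25%.
- 25% and 40%: pooled 32.5%.
- 20% and 46%: pooled 33.0%.

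**4. What the model could show if run.** In 400 simulated trials of 2,520 families, loss was 15% in one arm and 35% in the other, with three baseline covariates unrelated to dropout. The model without arm rejected in 4.8% of trials, its nominal error rate. With arm added, the arm term was significant in 100%. The one-third trigger was met in none.

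**5. What the trial could detect with arm included.** At pooled loss of 25% and 1,260 per arm, power reaches 80% for an arm difference of about 4.9 percentage points. It is 94% for 22% against 28% and above 99.9% for 20% against 30% (independent families assumed). These figures are for the arm main effect, not the interaction terms.

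**6. Illustrative bias.** If non-responders in each arm score g SD below responders, and a share m is missing, the responder mean exceeds the full-arm mean by g × m. The bias in FSP minus TAU is g × (m_FSP − m_TAU). Both g and the split are assumed; the document gives neither.
- FSP 20%, TAU 30%, g = 0.3: 0.3 × (−0.10) = −0.03 SD.
- Same split, g = 0.5: 0.5 × (−0.10) = −0.05 SD.
- Split reversed: +0.03 to +0.05 SD.

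In size this is 15% to 25% of 0.20. It ignores covariate adjustment. The standard error implied by the design is about 0.20/2.8 ≈ 0.07, so the bias in these examples is below one standard error.

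**The case against.** The strongest reply is that the regression does what it is said to do. Its stated purpose is to describe dropouts by background, and other parts of the plan protect the comparison. Much of this stands.

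- **Losses by arm would be visible.** The plan commits to CONSORT reporting, which normally shows losses by arm. A reader might infer that an imbalance would go unseen, and the document does not support that. Counts do not, however, show whether the type of family lost differs by arm.
- **Some correction is planned.** The ANCOVA adjusts for about eleven baseline variables. If loss depends only on arm and those variables, and the regression is correctly specified, much of the bias is removed. So a claim that nothing planned could correct the problem would also go too far. What remains is loss related to the outcome beyond those covariates.
- **TAU families are not left without contact.** It would be wrong to infer that they receive nothing. They are offered birth-preparation sessions, general practitioner and midwife visits and postnatal nurse home visits. Reminders, the telephone option and the prize lottery are not limited to FSP. TAU lacks only the FSP contact.
- **630 is expected dropout.** It is not a stated count of missing PSOC scores, because the article does not equate the two.
- **The bias figures are assumed**, and with greater TAU loss they run against FSP.

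It might also be said that attrition analysis belongs in a fuller analysis plan. That holds for sensitivity analyses, which are therefore only optional below. It does not hold for the threshold and the covariate set, because the article states both.

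**Conclusion.** The point holds in a limited form. The dropout analysis is fixed without arm and behind a threshold of 33.3%, while the plan expects 25%. At that expected loss it would almost surely not run. If run, it could not test whether loss, or its predictors, differ between arms. CONSORT counts and the ANCOVA reduce the consequence but do not supply that test.

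The textual finding is firm and does not depend on the recruitment target, since it compares 25% with one third. The effect on the trial result is not established: 0.03 to 0.05 SD is an illustration under assumed loss rates and score gaps, and its sign depends on which arm loses more. The primary analysis is not shown to be biased. This is a cheap improvement that should be made, not a flaw that undermines the trial.

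**What to change.** - Remove the one-third threshold and run the dropout analysis whatever the loss rate.
- For this analysis, define dropout as a missing nine-month PSOC, so that it means the same in both arms, and keep it separate from dropping out of the program. State whether mothers and partners are analysed separately.
- Add study arm and arm-by-baseline-covariate terms to the logistic regression, with a joint test of the interactions.
- Optionally, add one sensitivity analysis of the primary ANCOVA weighted by the inverse probability of response, using the linked register covariates. Register variables are preferable because financial strain and social desirability come from the survey and will be missing for families who skip the baseline questionnaire. This addresses only missingness explained by observed data.

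The cost is a little more analysis work. The register data are already to be linked, and design, recruitment and data collection do not change.

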### Dates defining periods of recruitment and follow-up

Recruitment began on November 24, 2014. Inclusion will continue at least until May 1, 2016. As detailed above, survey data will be obtained at four time points, during pregnancy, when the child is 9 months, 18 months, and 7 years. We will follow the families continuously through register-based data until the child turns 7 years old.

### Harms

The program consists of a network component (interaction with other couples who are also expecting their first child) and an information component provided by health professionals and others such as financial advisors, child dentists, and family counselors. There may be smaller inconveniences, at least for some, associated with the level of time consume from participating in a program such as FSP. As explained above, however, participation is entirely voluntary and will not affect access to other family services provided by the municipality or the region. Most meetings are held after 3 pm and 10 out of 12 are held from 4.30-6.30 pm. This is to minimize interference with families’ working lives. For all these reasons, we expect the intervention to be associated with very low risk for participants.

### Registration numbers and name of trial registry

The project is registered with Clinicaltrials.gov; ClinicalTrials.gov ID NCT02294968.

The project has been approved by the Regional Ethical Committee (Central Denmark Region); registration number ESDH 1-10-72-109-14.

The project has been approved by Danish data protection agency; registration number 2014-41-3016.

### Protocol availability

This protocol will be made available at www.econ.au.dk/familieivaerksaetterne.

## Discussion

The protocol describes an ambitious experimental evaluation of a universal group-based parenting support program that is currently being rolled out large scale in Denmark. Such an evaluation has not previously been made either in Denmark or internationally.

## Abbreviations

CPR: Central Personal Register
FSP: Family Startup Program
PSOC: Parental Sense of Competence
TAU: Treatment As Usual
